#### Secondary study endpoints and measures

Several secondary endpoints will further compare the intervention and control arms and document the feasibility and acceptability of the intervention (Table 6). Of note, some endpoints are collected all along the trial for process monitoring and assessment of the feasibility of the TB-Speed intervention. Among others, they include the *proportion of children with NPA and stool samples collected as per protocol* and the *time to sample collection and Xpert result after collection.*

**Table 6 Tab6:** Secondary endpoints

Endpoints	Measures	Time of measurement
***Secondary endpoints considered for a comparison between arms***		
TB diagnosis based on the clinician’s judgement	# of children diagnosed with TB based on the clinician’s judgement	Any time during the follow-up
TB treatment initiation	Proportion of children diagnosed with TB AND who with at least one TB treatment recorded	Any time during the follow-up
Time to TB treatment initiation	Date/Time of the 1st TB treatment – Date/Time of TB diagnosis (in hours)	Any time during the follow-up
Duration of TB treatment at end of trial	Number of days between date of TB treatment initiation and date of TB treatment end	Any time during the follow-up (week 12 or early termination)
Inpatient deaths	# of children who died after inclusion and before hospital discharge	Before discharge
Duration of initial hospitalization	Date of the 1st recorded discharge – Date of the 1st recorded admission (in days)	At the first discharge
Readmission following discharge	# of admission occurring after the 1st discharge	Any time during the follow-up
Weight gain	Proportion of weight gain at 12 weeks (as compared to body weight at inclusion)	At 12 weeks
Cost effectiveness	Incremental cost-effectiveness ratio (ICER) of intervention compared with WHO SOC, measured in cost per DALY averted	Lifetime, based on differences in mortality up to 12 weeks

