In high TB burden settings, there is growing evidence that TB is common in children with pneumonia [9]. Although TB is a chronic disease in adults, recent data shows that the duration of respiratory symptoms before admission can be acute in children with severe pneumonia associated with TB [10]. A systematic review showed that up to 23% of children admitted to hospital with an initial diagnosis of pneumonia were later diagnosed with TB [10, 11]. This is particularly true in the African and South-East Asian WHO regions, which accounted for 30 and 40% of all paediatric TB cases in 2019 respectively [1]. In these regions, the case fatality rate for childhood pneumonia associated with TB is high, ranging from 4 to 21% [10], with younger age, malnutrition and HIV infection increasing the risk of death [12, 13]. However, the diagnosis of TB in children with severe pneumonia remains low. Indeed, the current WHO standard of care (SOC) for young children with pneumonia considers a diagnosis of TB only if the child has a history of prolonged symptoms or fails to respond to antibiotics [14]. Therefore, many children with TB-associated severe pneumonia are currently missed or diagnosed too late, which is likely to affect their outcome.

In 2013, WHO updated its policy to include Xpert MTB/RIF (Cepheid, USA) as the initial test for the diagnosis of TB in children, based on a meta-analysis showing a pooled sensitivity and specificity of Xpert MTB/RIF performed on gastric lavages of 66% (95% confidence interval 51–81) and 98% (95% confidence interval 96–99), respectively, when compared with culture [15, 16]. Although data on the performance of Xpert MTB/RIF in children with pneumonia are limited, in Bangladesh, sensitivity on gastric aspirates or sputum samples compared to culture in this group was equivalent to that reported in other studies [17]. The next-generation of Xpert MTB/RIF assay, Xpert MTB/RIF Ultra (Ultra), has a lower detection threshold (similar to culture), which is expected to improve the diagnosis of children with paucibacillary TB [18, 19].

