Previous studies in Africa and Asia have shown that alternative specimen collection methods such as nasopharyngeal aspirates (NPA) and stool samples are easier to implement, and are better tolerated in young and sick children [20–24]. These methods do not require a child to fast, as mandatory for gastric aspirates, and are more suitable than induced sputum in children with severe respiratory deficits [25]. Recent studies have shown similar sensitivity of Xpert MTB/RIF on the combination of one stool and one NPA as compared to two induced sputum or two gastric aspirates [20, 26].

We therefore propose a diagnostic trial to assess the impact on mortality of adding the systematic early detection of TB using Ultra performed on NPA and stool samples to the WHO SOC for children with severe pneumonia, followed by immediate initiation of anti-TB treatment in children testing positive on any of the samples. Our hypothesis is that in high TB burden countries, testing young children with severe pneumonia for TB and starting those who test positive on anti-TB treatment on the day of presentation, could reduce all-cause mortality through reduction of mortality attributed to TB.

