## Methods

### Aim

The primary objective of the TB-Speed Pneumonia trial is to evaluate the impact on all-cause mortality at 12 weeks post inclusion of adding systematic early detection of TB with Ultra, performed on one NPA and one stool sample in young children with severe pneumonia, followed by immediate anti-TB treatment initiation in children with a positive Ultra result, in high TB incidence countries, as compared to the WHO SOC alone. The study only includes children with community-acquired pneumonia, excluding children already hospitalized who have developed a nosocomial pneumonia.

Secondary objectives will assess the impact of the systematic TB detection on TB case detection, time to TB treatment initiation, inpatient mortality, duration of initial hospitalization and hospital readmission rate, and will assess the feasibility and acceptability of the intervention.

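### Time to TB treatment initiation is clocked from TB diagnosis, so the between-arm comparison omits the admission-to-diagnosis delay that the intervention is designed to shorten

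*Protocol article*

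**What the plan says.** The Aim section states that the secondary objectives "will assess the impact of the systematic TB detection on TB case detection, time to TB treatment initiation, inpatient mortality", among others. The Background gives the reason. Under the standard of care, "many children with TB-associated severe pneumonia are currently missed or diagnosed too late, which is likely to affect their outcome". The hypothesis is that testing young children with severe pneumonia and "starting those who test positive on anti-TB treatment on the day of presentation, could reduce all-cause mortality".

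In Table 6, under "Secondary endpoints considered for a comparison between arms", the measure for time to TB treatment initiation is "Date/Time of the 1st TB treatment – Date/Time of TB diagnosis (in hours". The row above it, TB treatment initiation, is measured as "Proportion of children diagnosed with TB AND who with at least one TB treatment recorded".

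The section on the TB-Speed intervention places Ultra testing on the day the child is admitted. It sets a 3 h target for turnaround of results and has drugs at hand in the ward. The section on the WHO standard of care has TB evaluated when cough and fever have lasted more than two weeks and signs of pneumonia remain after antibiotics. It also allows earlier molecular testing on clinical suspicion. Note d to Table 5 allows treatment on strong clinical suspicion in both arms.

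**The concern.** The objective asks whether systematic detection brings treatment forward. The intervention does this mainly by bringing diagnosis forward, and a clock that starts at diagnosis cannot register that part. A control child diagnosed late and treated at once scores close to zero, and the late diagnosis leaves no trace.

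The measure also exists only for children who were both diagnosed and treated. The intervention is expected to change who they are. Control children whose TB is missed, one of the two harms the Background names, contribute nothing.

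At stake is the answer to one named secondary objective. If the mortality result is null, readers will ask whether treatment really started earlier in the intervention arm. The endpoint as defined does not tell them, and on some intervals it would point the wrong way.

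**Working it through.** The article states no figure for this endpoint, so there is nothing to reproduce. The check is a decomposition, then an illustration.

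**Decomposition.** For a child who is diagnosed and then treated, let A be the time from admission to diagnosis and B the time from diagnosis to first TB treatment.

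- Time from admission to treatment = A + B.
- Table 6 measure = B.
- Arm difference (intervention minus control) on the Table 6 clock = B_int − B_ctl.
- Arm difference from admission = (A_int + B_int) − (A_ctl + B_ctl).

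A does not appear in the third line. The sign of the Table 6 comparison depends on B alone, however large the difference in A. This holds whatever the interval lengths are.

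**Where the arms are expected to differ.** The intervention section puts detection on the admission day. The standard-of-care section ties evaluation largely to prolonged symptoms or failure of antibiotics. The expected contrast is therefore mainly in A.

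**Illustration.** All intervals are assumptions, in hours. Negative differences favour the intervention.

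| Case | Control A, B | Intervention A, B | Table 6 clock | From admission |
|---|---|---|---|---|
| 1 | 168, 2 | 3, 3 | 3 − 2 = +1 | 6 − 170 = −164 |
| 2 | 168, 0 | 3, 3 | 3 − 0 = +3 | 6 − 168 = −162 |
| 3 | 336, 0 | 24, 6 | 6 − 0 = +6 | 30 − 336 = −306 |
| 4 | 72, 1 | 6, 2 | 2 − 1 = +1 | 8 − 73 = −65 |
| 5 | 72, 12 | 6, 2 | 2 − 12 = −10 | 8 − 84 = −76 |

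In cases 1 to 4, a gain of 65 to 306 h from admission shows as 1 to 6 h in favour of control. In case 5 the direction is right, but a 76 h gain shows as 10 h. Reversal occurs exactly when B_ctl < B_int.

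**The subset.** The Power and sample size section assumes that detection rises from 15 to 50% between arms. Reading this as a share of children with TB, for every 100 such children about 15 could enter the comparison in control and 50 in the intervention arm, a ratio of 50/15 = 3.3. The 85 and 50 who are missed have no value. The two groups compared would therefore differ in how they were selected as well as in how they were managed.

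**Whether another endpoint fills the gap.** The turnaround endpoints are assessed in the intervention group only and start at sample collection. Duration of TB treatment at end of trial depends partly on the start date for children still on treatment at week 12, but death or early stopping cuts it short. No between-arm endpoint runs from admission or inclusion to diagnosis or treatment.

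**The case against.** The strongest defence is that the strategy has two parts, early detection and immediate treatment of positives, and that the diagnosis-to-treatment interval evaluates the second. That stands. The measure is informative about immediate initiation and is worth keeping. It does not answer the objective as the Aim section words it.

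A reader might infer that the endpoint cannot show faster treatment at all. The documents do not support that: it can show faster starts after diagnosis, as in case 5.

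A reader might also infer that it will favour control. That is not established either. The article gives no intervals and does not define the date/time of diagnosis. Control clinicians may use Xpert or Ultra, so a control diagnosis can be bacteriological with a real gap before treatment. Treatment on clinical suspicion is open to both arms, so near-zero intervals can occur in either. The two weeks of symptoms in the standard of care may partly precede admission, so the control delay after admission is also unknown.

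On TB treatment initiation, the wording is ambiguous. It can mean the proportion treated among diagnosed children, or the proportion of all children who were both diagnosed and treated. The second reading would already use all enrolled children, so the point there is one of clarity.

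Finally, the article ranks this endpoint no higher than the other secondary endpoints, and the Data analysis section rests the conclusion on the mortality odds ratio alone. That limits the seriousness. Details such as the handling of competing events may properly sit in the statistical analysis plan, and their absence from the article is not the complaint. The starting point of the clock is stated in the article, and it is the starting point that does not fit.

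**Conclusion.** The point holds. As defined, the endpoint leaves out the admission-to-diagnosis interval, which the Background and the description of the intervention identify as the target, and no other between-arm endpoint restores it. That conclusion follows from the definition and needs no assumption.

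The size does rest on assumptions. A real gain in time to treatment can be missed or much reduced, and the comparison favours control only if control intervals from diagnosis to treatment are the shorter ones. The cases shown give 1 to 6 h against the intervention, or 10 h for it, where the gain from admission is 65 to 306 h or 76 h.

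Nothing in the documents makes this the main mechanistic endpoint, and the primary endpoint, its analysis and the sample size are untouched. It should be fixed, but it is not a condition for the validity of the primary result.

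**What to change.** 1. Define time to TB treatment initiation as first anti-TB treatment minus hospital admission or inclusion. Table 6 already uses the date/time of first treatment and the date of admission. The article does not show that the clock time of admission is recorded. If it is not, report in days.
2. Compare it over all enrolled children in each arm, for example as cumulative incidence of treatment initiation to week 12 with death as a competing event. Moving the clock without widening the population would leave the selection problem in place.
3. Keep diagnosis-to-treatment time as a labelled process measure of immediate initiation, and define the date/time of diagnosis.
4. Reword TB treatment initiation so that its denominator is clearly all enrolled children.

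The cost is slightly more analysis work and possibly coarser time units. By the Trial status section, last follow-up was planned for December 2020, before the article appeared in March 2021, so the change would come after planned data collection. It should therefore be written and dated in the statistical analysis plan that the IDMC validates before analysis, with the Table 6 measure still reported alongside.

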### Study visits and assessments

After written informed consent is obtained from parent(s)/guardian(s) by the study clinician or study nurse, the baseline visit includes a complete clinical evaluation, a digitalized chest X-ray (CXR), HIV and malaria testing, and a complete blood count. For children in the intervention arm, initial bacteriological specimen collection is done as soon as possible and within 24 h of hospital admission, including one NPA collected by the nurse on the day of admission, and one stool sample collected as soon as the child is able to produce stool. Additionally, blood samples and leftovers from NPA and stool are collected for future biomarkers studies in children for whom parent(s)/guardian(s) give their consent for biobanking. Data about routine care as well as additional study strategies are collected. All children are followed up for a total duration of 12 weeks, with four systematic protocol visits planned at day 3 (and/or at hospital discharge), 2 weeks after discharge (as recommended by the WHO SOC), and 12 weeks after recruitment. Each follow-up visit comprises a clinical evaluation, and collection of medical history since the last visit, an evaluation of adherence to TB treatment if initiated, and TB drug prescription and dispensation to cover the time until the next visit (Table 5). Parent(s)/guardian(s) are invited to bring their child back to the hospital in case of new symptoms for an unscheduled (extra) visit. During the final visit at 12 weeks, a second digital CXR is performed, as well as an assessment of TB disease evolution and TB treatment outcome in those diagnosed with TB (improvement, treatment failure, death, or lost to follow-up).

**Table 5 Tab5:** Study assessments and specimen collection

	Inclusion (Day 0)	Day 3	Discharge	2 Weeks Post-Discharge	(Extra visit)^**i**^	Week 12

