**ADDITIONAL STUDY ASSESSMENT AND PROCEDURES (control and intervention arm)**						
Eligibility screening	X					
Clinical evaluation^e^	X	X	X	X	(X)	X
Medical history	X	X	X	X	(X)	X
Digital chest X-Ray	X				(X)	X
Safety assessment	X	X	X	X	(X)	X
TB drug adherence assessment		(X)	(X)	(X)		(X)
TB treatment response				X		X
HIV test^f^	X					
Malaria test	X					
Complete blood count	X					
Biobank: plasma, whole blood^g^	X					

*WHO* World Health Organization, *TB* tuberculosis, *NPA* nasopharyngeal aspirate

^a^See Table 4

^b^According to national treatment guidelines based on WHO recommendations

^c^In children with a clinical suspicion of TB (chronic symptoms, failure to respond to antibiotic treatment or TB exposure), TB will be evaluated using routine procedures. This can include Xpert MTB/RIF or Ultra (depending on local availability) on standard bacteriological samples as usually implemented at the ward

^d^In the intervention arm, TB treatment will be initiated immediately in case of a positive Ultra result. In both arms, TB treatment could be initiated in case of a strong clinical suspicion

^e^Content of clinical evaluation varies with the visit; includes TB exposure and symptoms assessment at inclusion

^f^Performed if not available in the patient medical chart. In Côte d’Ivoire, should be discriminant for HIV 1 and 2

^g^In children < 18 months weighing < 5 kg, or presenting with signs of severe anaemia (conjunctival or palmar pallor): plasma sample for biobank will not be collected. Overall, volume of blood draw must not exceed 3 ml/kg/visit and 7 ml/kg/6 weeks

^h^In a subset of children only

^i^An extra TB visit will be performed if the child presents with signs and symptoms in favour of a presumptive TB

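### TB treatment duration, cut at week 12 after recruitment and defined only in treated children, cannot be interpreted as a between-arm comparison

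*Protocol article*

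**What the plan says.** Table 6 of the protocol article has a block headed "Secondary endpoints considered for a comparison between arms". One of its rows is "Duration of TB treatment at end of trial". The measure is "Number of days between date of TB treatment initiation and date of TB treatment end", and the time column adds that it is taken at week 12 or at early termination.

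Study visits and assessments fixes the clock: "All children are followed up for a total duration of 12 weeks", with the last visit 12 weeks after recruitment. At that visit the TB treatment outcome is classed as "improvement, treatment failure, death, or lost to follow-up"; no category stands for a completed course. Table 5 still allows TB treatment and an adherence check at week 12. Its footnotes leave treatment to national guidelines, so the article gives no course length.

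On the start of treatment, a Table 5 footnote says: "In the intervention arm, TB treatment will be initiated immediately in case of a positive Ultra result". Both arms may also start treatment on strong clinical suspicion. The Background explains that under standard of care TB is considered only after prolonged symptoms or failure of antibiotics.

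**The concern.** A child still on treatment at the last visit has no date of treatment end. The only date available is the end of follow-up, which is counted from recruitment. The recorded duration is then set by how long after inclusion treatment began, which is what the intervention is designed to change. Death also cuts the duration short, and mortality is the outcome that the trial expects to differ between arms.

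The measure exists only in treated children. Power and sample size assumes that detection rises from 15 to 50% between control and intervention, and the Discussion expects more empirical treatment under the intervention. The two treated groups are therefore selected differently, and randomising the order of the hospitals does not make them comparable.

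At stake is the reading of one secondary result. A longer mean duration under the intervention could be taken for better continuity of treatment when continuity is the same.

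**Working it through.** **Plan's own figure.** The article gives none for this endpoint. The sample size concerns mortality only (1730 × 2.16 / 0.99 ≈ 3775, against 3780 stated) and is not touched.

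**Inputs from the article.** Follow-up of 12 × 7 = 84 days from recruitment; overall mortality of 15% (control) and 10.5% (intervention).

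**Assumptions not in the article.** Exponential start delay after inclusion, mean 1 day (intervention) and 14 days (control); the overall mortality rates applied to treated children, with death on average 14 days after start; no other stopping; the same prescribed course in both arms.

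**Step 1: definition.** Observed duration = min(84, day of death, stop or loss, start day + course length) − start day. If the course is at least 84 days and the child stays on treatment, this is 84 − start day:
- start on day 0: 84 days
- start on day 14: 70 days
- start on day 28: 56 days

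A child who starts on day 0 and dies on day 5 scores 5 days.

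**Step 2: expected arm difference.** By hand, ignoring small truncation effects, mean duration ≈ (1 − p) × (84 − mean delay) + p × 14, where p is the proportion dying:
- intervention: 0.895 × 83 + 0.105 × 14 = 74.3 + 1.5 ≈ 75.8
- control: 0.85 × 70 + 0.15 × 14 = 59.5 + 2.1 = 61.6
- control with p = 10.5%: 0.895 × 70 + 0.105 × 14 = 62.7 + 1.5 ≈ 64.1

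Simulation gives about 75.7, 61.6 and 64.2 days for courses of 84 to 180 days. The gap is about 14 days with identical prescribed treatment. Of this, 75.7 − 64.2 = 11.5 days come from the start delay and 64.2 − 61.6 = 2.6 days from deaths. In these simulations no child completes the course.

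**Step 3: other influences.** With a 168-day course, assigning 10% or 30% of intervention children a stop on a uniformly random day of the course lowers their mean from 75.7 to 73.9 or 70.3, that is by 1.8 or 5.4 days. Early stopping therefore moves the measure, but even at 30% by less than the assumed start delay does.

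**Step 4: dependence on course length.**

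| Course (days) | Intervention mean | Control mean | Gap |
|---|---|---|---|
| 28 | 26.3 | 25.4 | 0.9 |
| 56 | 51.5 | 48.0 | 3.5 |
| 84 to 180 | 75.7 | 61.6 | 14.1 |

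The artefact is large only if the course runs to about week 12 or beyond.

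**The case against.** The strongest reply is that the row's title and time column disclose the cut-off. Read as written, it is treatment received within the trial, which ought to be longer when treatment starts earlier. The article never calls it continuity, does not name it among the secondary objectives, gives a model only for mortality and rests its conclusion on the mortality odds ratio. Rules for ongoing treatment and death may stand in the statistical analysis plan, which is not shown.

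Much of this is fair and limits the weight of the point. It does not remove it. The row is listed for comparison between arms, and Data analysis has all results reported as effect estimates with 95% confidence intervals. A censoring rule would settle the missing end date but not the selected group of treated children.

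Three stronger readings are tempting, and the documents do not support them.

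- *The row duplicates time to TB treatment with the sign reversed.* It does not. Table 6 counts that endpoint from TB diagnosis, whereas duration at week 12 depends on the delay from inclusion. A child diagnosed on day 28 and one diagnosed on day 0, each treated within 2 hours, score the same 2 hours on that row but about 56 and 84 days here.
- *Duration reflects nothing but start day and death.* Stopping, withdrawal and loss also shorten it, as Step 3 shows.
- *Treatment is known to continue past week 12.* The absence of a completion category and the allowance for TB treatment at that visit point that way, but no course length is given.

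**Conclusion.** The point holds as a minor one. The measure is fixed on a recruitment-based clock, in a group that the intervention alters, and is offered as a comparison between arms. If the course runs to week 12 or beyond, the difference mainly reflects start day relative to inclusion, case mix and survival, with early stopping and loss also contributing.

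Under the assumptions above the gap is about 14 days with no difference in prescribed treatment or stopping. The delays of 1 and 14 days, the time to death and the use of overall mortality in treated children are illustrative, so the figure shows an order of size and is not a forecast. Differences in case mix are not quantified. The primary endpoint and its conclusion are unaffected.

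**What to change.** Move the row out of the between-arm block of Table 6. Report it descriptively by arm as days on TB treatment up to week 12, showing separately the children still on treatment at the cut-off, those who stopped for other reasons, those who died and those lost. State that no conclusion about treatment continuity will be drawn from the arm difference.

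The proportion of treated children still on treatment at week 12 would not cure the problem: a child who starts on day 0 has 84 days in which to stop and one who starts on day 28 has 56, and only treated children count. If continuity is of interest, describe retention at a fixed time after treatment start among children with that much follow-up available, with death as a separate outcome. For example, retention at 28 days can be described for every child who starts by day 84 − 28 = 56. This too remains descriptive.

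The cost is one table row, matching wording in the statistical analysis plan and the loss of one inferential secondary comparison. No new data are needed.
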